## Sites and site monitoring

The study will be conducted at up to five sites within the UK and monitored according to the standard operating procedure for site monitoring of the GSTT Trials Unit, which includes at least one site visit over the course of the trial as well as triggered visits if required. All data from the sites will be shared solely with the co-ordinating centre. Local sites will liaise directly with the manufacturers for equipment/disposables. The lead site will supervise all other aspects of the study and is available 24 h, 7 days for questions relating to the study. The randomisation sequence is solely held at the lead centre who will also allocate trial participant numbers. All sites are University-affiliated hospitals with tertiary intensive care units experienced in the provision of extracorporeal CO_2_ removal. Current sites include Guy’s and St Thomas’ NHS Foundation Trust, Manchester University NHS Foundation Trust, Chelsea and Westminster NHS Foundation Trust and Queen Elizabeth University Hospital, Glasgow. Additional data about sites can be obtained from the corresponding author. Source data verification conducted over the course of the trial will be at least 1% and will increase if significant discrepancies are found.

## Protocol amendments

Protocol amendments will be approved by both the sponsor and the REC prior to being implemented. Any protocol amendments will be numbered and dated and shared with investigating centres to ensure version control.

## Data and data monitoring

The study will be conducted in accordance with the current approved protocol, ICH GCP, relevant regulations and standard operating procedures. Audits of data are not planned.

Regular monitoring will be performed according to ICH GCP. Data will be evaluated for compliance with the protocol and accuracy in relation to source documents. Following written standard operating procedures, the monitors will verify that the clinical trial is conducted and data are generated, documented and reported in compliance with the protocol, GCP and the applicable regulatory requirements.

Data will be stored in the department of Critical Care, Guy’s and St Thomas’ NHS Foundation Trust.

## Access to data

Direct access will be granted to authorised representatives from the sponsor, host institution and regulatory authorities to permit trial-related monitoring, audits and inspections. The funder has access only to anonymised information embedded within the device which is not accessible to researchers. All other data remain the property of the researchers.

## Statistical analysis

Summary measures for the baseline characteristics of each group will be presented as mean and standard deviation for continuous (approximate) normally distributed variables, medians and interquartile ranges for non-normally distributed variables, and frequencies and percentages for categorical variables. The planned primary efficacy analyses, difference between the two arms in reduction in NIV duration, will be analysed on randomized patients using a non-parametric approach, Mann-Whitney U test. Similar analyses as for the primary outcome measure will be conducted for secondary efficacy data. Missing data in the efficacy population will not be interpolated. All randomised participants in both arms with valid non-invasive ventilation data will be included in the analysis. Analysis of the physiological data will be per protocol, whilst analysis of outcomes will be intention to treat. Physiological data will be compared within individuals to describe a relative change in work of breathing. The statistical analysis plan can be accessed through the corresponding author. No subgroups have been planned.

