## Background

Chronic obstructive pulmonary disease (COPD) is a syndrome characterised by progressive and not fully reversible expiratory airway flow limitation. The underlying pathophysiology of COPD is the progressive destruction of the elastic and alveolar tissue within the lung, resulting in reduced expiratory flow rates, maldistributed ventilation, gas trapping and hyperinflation, which in turn lead to diaphragmatic flattening and inefficient respiration. COPD is punctuated by recurrent exacerbations characterised by a worsening of the patient’s dyspnoea, cough and/or sputum production beyond day-to-day variations [1]. Acute exacerbations are an important cause of hospital admission and impact on patients’ quality of life [2–5], as well as having a huge societal impact amounting to ~ 6% of the total healthcare cost [6]. Exacerbations also accelerate disease progression, leading to a progressive stepwise functional decline [7–13].

Patients with significant exacerbations of COPD resulting in hypercapnic respiratory acidosis (PaCO_2_ > 6 kPa (45 mmHg) and pH < 7.35) have life-threatening respiratory failure and non-invasive ventilation (NIV) has significant mortality benefits for patients [1, 14–19]. NIV provides both inspiratory and expiratory pressure, which, by splinting open collapsing airways by matching intrinsic positive end expiratory pressure (PEEP) and providing positive pressure to assist tiring respiratory muscles, enhances ventilation. This enables an improved ventilation–perfusion relationship, improves gas exchange and simultaneously reduces oxygen consumption and carbon dioxide production because of the reduction in work of the respiratory muscles [16, 20]. Although NIV has substantially improved mortality (risk ratio 0.54, 95% CI 0.38 to 0.76) and decreased the need for intubation (risk ratio 0.36; 95% CI 0.28 to 0.46) in patients with an acute exacerbation of COPD [16], 15–30% of patients commencing NIV fail and require intubation and mechanical ventilation [21–23]. Risk factors for NIV failure include obtundation, hypercapnoea, persisting respiratory acidosis (pH < 7.30), higher APACHE II score (> 28), tachypnoea (> 29) and lack of improvement in the first 1–2 h of therapy [23–27]. Patients who fail NIV and require intubation have a significantly higher mortality than those who improve with NIV (30% vs < 10%) [28], with mortality rates up to 57% in some case series [29].

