## Methods/design

### Design

The trial is a prospective, randomised, controlled, with 1:1 allocation ratio unblinded study of ECCO_2_R in adults with AECOPD at risk of failing NIV as demonstrated by a persisting pH < 7.30 due to hypercapnoea after initial medical therapy and at least 1 h of NIV. The study will randomise a total of 24 patients, 12 in each treatment arm. Allocation was generated by computer-generated random number and concealed via opaque sealed envelopes.

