### Inclusion criteria

Known COPD with an acute exacerbation. An acute exacerbation is defined as per the GOLD criteria as an increase in dyspnoea, cough and/or sputum over the patient’s normal symptoms. A severe exacerbation is defined as one requiring hospital admission. Patients are known to have COPD when they have a previous diagnosis made and recorded on their medical records, data in support of this will include chest imaging, pulmonary function tests and clinical history/examination.Patients with a persistent arterial pH < 7.30 due primarily to hypercapnic respiratory failure after standard medical therapy and at least 1 h of NIV.Age over 18

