### Primary outcome

The primary outcome is the time taken to discontinuation of NIV in patients with acute, severe exacerbations of COPD through the addition of ECCO_2_R to standard care. The definition of discontinuation of NIV is cessation of NIV for at least 6 h. Time to discontinuation will be measured from randomisation. The reason for discontinuation will be collected and successful discontinuation consists of being free of mechanical ventilation.

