### Secondary outcome

Secondary outcomes include the impact of ECCO2R on:Safety, including:Incidence of haemorrhagic complications—significant haemorrhage is defined as bleeding requiring transfusion of more than one unit of blood, intracerebral bleeding, bleeding requiring procedural interventionIncidence of thrombosis—all patients will have screening duplex ultrasound of the cannulated vesselIncidence of haemolysis defined by rising lactate dehydrogenase, bilirubin red cell fragments on a blood film and/or a rising plasma free-haemoglobin (> 0.5 g/dL)Complications relating to cannulation including those at insertion—bleeding, vascular damage, pneumothorax and line infection, both clinically apparent (erythema/cellulitis at insertion site) and microbiologically proven (positive blood culture with concomitant line tip culture or line insertion site culture)Physiology, including respiratory rate, heart rate, blood pressure, temperature, arterial blood gases measured at time (T)0 min, T30 minutes, T 60 min, then every fourth hour for the first 24 h and then every sixth hour until discontinuation of the acute phase of the trialDaily spirometry including forced vital capacity, forced expiratory volume in 1 s and the ratio between themWork of breathing, including electrical impedance tomography, parasternal electromyography and oesophageal pressure (these are described in detail below)Patient outcomes:Mortality (ICU, hospital and 3 month)Length of stay (ICU, hospital)Need for intubation and where this occurs, duration of mechanical ventilation and need for tracheostomy, NIV failure and need for intubation will be decided by the clinical team managing the patient. Reason for NIV failure will be recorded by the research team.3-Month hospital readmission rateTolerance, assessed using both a numerical rating scale (0–10) and visual acuity scale (0–10 cm) for both dyspnoea and comfort with the lowest reading being extremely uncomfortable and the highest being extremely comfortable. Comparisons between the two different measures will be used without an absolute definition of comfort/discomfort.At 3-months following randomisation: COPD assessment test, St George’s Respiratory Questionnaire, EuroQoL 5D. Comparisons between the different measures will be used without an absolute definition of success at follow-up.Cost-effectiveness with ICU bed day and consumables cost/quality adjusted life year (QALY)

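### The primary Mann-Whitney test makes no use of baseline arterial pH; pre-specifying adjustment for it would cost little and could gain power if pH is at least moderately prognostic

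*Protocol article*

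**What the plan says.** Under Statistical analysis, the difference between arms in NIV duration "will be analysed on randomized patients using a non-parametric approach, Mann-Whitney U test". No covariate is named. The outcome is a duration: "Time to discontinuation will be measured from randomisation" (Primary outcome).

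The Design section describes an open trial "with 1:1 allocation ratio unblinded study". That section and Randomisation and codebreaking describe a computer-generated list held in sealed envelopes. Neither states stratification by severity.

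Baseline pH is available in everyone. Entry is limited to "Patients with a persistent arterial pH < 7.30 due primarily to hypercapnic respiratory failure after standard medical therapy and at least 1 h of NIV" (Inclusion criteria), and the Secondary outcome section schedules "arterial blood gases measured at time (T)0 min, T30 minutes" and onwards. On prognosis, the Background says: "Risk factors for NIV failure include obtundation, hypercapnoea, persisting respiratory acidosis (pH < 7.30", followed by APACHE II score, tachypnoea and lack of early improvement.

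The Sample size section claims 80% power with 12 per arm for a 12 h difference in means, SD 10 h and alpha 5%. A separate analysis plan exists but is not shown.

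**The concern.** As described, neither the allocation nor the named primary test takes account of how acidotic a patient is at entry, although that value is already recorded. This could matter in two ways.

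- **Power.** If pH explains part of the variation in NIV time, an unadjusted test leaves that variation in the error term.
- **Chance imbalance.** With 12 per arm, a noticeable difference in mean pH is quite likely and would carry into the observed difference in NIV time. The trial is open label and NIV is stopped on the clinician's judgement, so an adjustment chosen after the imbalance had been seen would carry little weight.

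**Working it through.** **Inputs from the article:** 12 per arm, difference 12 h (48 h to 36 h), SD 10 h, alpha 5%. The article does not say whether alpha is one- or two-sided; two-sided is used because it reproduces the stated power. **Assumptions:** normal outcome and covariate, and a correlation r (absolute value) between baseline pH and NIV duration, varied from 0 to 0.5 because the article gives none.

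**Step 1: the stated power.** Two-sample t-test: noncentrality = 12 / (10 × √(2/12)) = 2.94 on 22 df, power 80.2%. The stated 80% is reproduced.

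**Step 2: the named test.** The exact Mann-Whitney test at 12 per arm rejects for U ≤ 37 or U ≥ 107. Its attained size is 4.5% and its simulated power on the same inputs is about 76.6%. This shortfall comes from the rank test and its discreteness. It is unrelated to pH: an adjusted rank test at r = 0 has the same shortfall.

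**Step 3: power with adjustment** (simulation, 20,000 trials per setting, ANCOVA on ranked outcome and ranked pH, nominal 5%):

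| r | Mann-Whitney | Rank ANCOVA | Gain (points) |
|---|---|---|---|
| 0 | 76.6% | 76.7% | 0.1 |
| 0.1 | 76.3% | 76.7% | 0.4 |
| 0.2 | 76.7% | 78.2% | 1.5 |
| 0.3 | 76.7% | 79.7% | 3.0 |
| 0.4 | 76.4% | 82.0% | 5.6 |
| 0.5 | 76.6% | 85.9% | 9.3 |

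Null rejection was 4.1 to 4.6% for Mann-Whitney and 4.9 to 5.3% for rank ANCOVA. Quade's version (compare residuals of ranked NIV time on ranked pH) gave about 76%, 77 to 78%, 79%, 82 to 83% and 85% at r = 0, 0.2, 0.3, 0.4 and 0.5. At r = 0 its loss was under 1 point.

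**Step 4: matched size.** Part of the gain in Step 3 is extra alpha, since the exact Mann-Whitney test spends only 4.5%. With Quade's test also run at nominal 4.49% (40,000 trials per setting), power against Mann-Whitney was 74.8% v 76.5% at r = 0, 75.9% v 76.3% at 0.2 and 78.1% v 76.6% at 0.3. That is a loss of about 2 points at r = 0 and a gain of about 1.5 at r = 0.3.

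**Step 5: chance imbalance.** SD of the between-arm difference in mean pH = √(2/12) = 0.41 SD of pH. P(|difference| > 0.5 SD) = 2 × [1 − Φ(0.5/0.41)] = 22%; for more than 1 SD it is 1.4%. The shift in the NIV difference from a 0.5 SD imbalance is 0.5 × r × 10 h:

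- r = 0.1: 0.5 h (4% of the 12 h target)
- r = 0.3: 1.5 h (12.5%)
- r = 0.5: 2.5 h (21%)

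**Step 6: effect of the entry cut-off.** Restricting the range of pH lowers a correlation to r·u / √(1 − r² + r²u²), where u is the ratio of restricted to unrestricted SD. As an illustration, assume pH is normal and entry takes the lowest 50% (u = 0.60) or 30% (u = 0.51). Then r = 0.3 becomes 0.19 or 0.16, and r = 0.5 becomes 0.33 or 0.28.

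**The case against.** The strongest case against is that nothing here is wrong. A Mann-Whitney test in a randomised trial is valid, its type I error is held, and its null distribution already allows for chance imbalance. This stands.

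The evidence that pH matters is also indirect. The Background links it to NIV failure, whereas the primary outcome is time to stopping NIV. Worse acidosis could prolong NIV or end it early through intubation, so the net correlation could be near zero. The factor cited, pH below 7.30, is met by every patient; only the spread below the cut-off remains, and Step 6 shows that this may push the correlation down. That all patients are enrolled on pH is therefore no evidence that pH predicts duration within the trial. This stands too. It is why the gain must be stated as conditional.

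The choice of pH over the other listed risk factors is a judgement. It is the one the article guarantees in every patient.

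The unseen analysis plan may contain an adjusted supporting analysis. It cannot be assumed to replace the primary test that the article names.

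A reader might infer that leaving out pH explains why the planned test has about 76% power rather than the stated 80%. Step 2 rules this out. A reader might also infer that the plan certainly loses power, or that its result would be biased. The first needs a correlation the article does not give; the second is false under randomisation.

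**Conclusion.** The point holds as a recommendation on efficiency and protection against chance imbalance, not as an error or contradiction. The likely benefit is small to moderate: negligible for correlations up to about 0.2, about 3 points of power at 0.3 and 8 to 9 at 0.5, with the entry cut-off making the lower end more plausible. The possible loss is smaller: under 1 point at nominal 5%, about 2 points at matched size. An imbalance large enough to move the estimate by 0.5 to 2.5 h (correlations 0.1 to 0.5) has roughly a one in five chance. These figures rest on the article's 12 h and 10 h, normal data and an assumed correlation. The change is worth making because it uses data already collected and has to be fixed in advance to be credible.

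**What to change.** Pre-specify the primary test as a rank-based ANCOVA (Quade): rank NIV time across all patients, regress it on ranked baseline pH, and compare the residuals between arms. Use one covariate only, the last arterial pH before allocation. A permutation p-value is optional if exactness is wanted. Keep the unadjusted Mann-Whitney test, with a Hodges-Lehmann difference and 95% CI, as the sensitivity analysis.

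This takes a sentence in the protocol and one in the analysis plan. It needs no new measurements and no more patients; the cost is the small power loss above if pH proves uninformative. The text should not present the adjustment as the remedy for the gap between about 76% and the stated 80%, which is a separate sample-size matter.

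### Extending the Mann-Whitney rule to secondary efficacy data can score an early death as a short stay, and it suits yes/no outcomes poorly

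*Protocol article*

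**What the plan says.** In the Statistical analysis section, the primary comparison "will be analysed on randomized patients using a non-parametric approach, Mann-Whitney U test". The section then states: "Similar analyses as for the primary outcome measure will be conducted for secondary efficacy data". On missing values it says: "Missing data in the efficacy population will not be interpolated". On analysis sets it says: "Analysis of the physiological data will be per protocol, whilst analysis of outcomes will be intention to treat". Physiology has its own rule: "Physiological data will be compared within individuals to describe a relative change in work of breathing". No other between-arm method is named, and no effect measure for any secondary outcome.

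The Secondary outcome section lists outcomes of different kinds under patient outcomes:
- Durations that death can cut short: "Length of stay (ICU, hospital", and duration of mechanical ventilation.
- Yes/no outcomes: "Mortality (ICU, hospital and 3 month", intubation, tracheostomy and 3-month readmission.

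The article does not say how a patient who dies enters the durations.

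**The concern.** The Mann-Whitney test ranks whatever number it is given. A stay that ends in death on day 2 is an observed, short value, so the missing-data rule does not catch it and it ranks among the best results. If early mortality differs between the arms, by treatment effect or by chance, the length-of-stay comparison moves in favour of the arm with more deaths. With 12 patients per arm, a few deaths are enough to do this.

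On a 0/1 outcome, a rank test answers a question that is better put as a difference in proportions. The location shift usually reported with it can be zero when the event rates clearly differ. At this sample size the p-value also depends heavily on how it is calculated.

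**Working it through.** **The plan's own figure.** The article gives no figure for the secondary analyses. Its one power statement is for the primary outcome: 12 per arm, difference 12 h, SD 10 h. The noncentrality is (12/10) × √(12/2) = 2.94 on 22 degrees of freedom, which at two-sided 5% gives 80.2% power by t-test. The stated 80% reproduces, and this point does not affect it.

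**Inputs for durations.** The Background gives mortality of under 10% in patients who improve on NIV, 30% in those who fail and are intubated, and up to 57% in some series. These are not trial-arm rates, so the values below are assumptions from that range. Also assumed: stay is counted to death, survivors' stays have the same distribution in both arms, and so do times to death.

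**Formula.** Let m_C and m_E be mortality on control and ECCO2R. Let q be the probability that a patient who dies has a shorter stay than one who survives. With ties counted as half, the probability that the ECCO2R patient has the shorter stay is

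m_E(1 − m_C)q + m_C(1 − m_E)(1 − q) + 0.5[m_E·m_C + (1 − m_E)(1 − m_C)] = 0.5 + (m_E − m_C)(q − 0.5).

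With every death ranked worst, the probability that ECCO2R does better is 0.5 − (m_E − m_C)/2.

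| Control deaths | ECCO2R deaths | q | Raw stay ranked | Deaths ranked worst |
|---|---|---|---|---|
| 10% | 30% | 1 | 0.60 | 0.40 |
| 25% | 10% | 1 | 0.425 | 0.575 |
| 10% | 57% | 1 | 0.735 | 0.265 |
| 10% | 10% | any | 0.50 | 0.50 |
| 10% | 30% | 0.79 | 0.56 | 0.40 |
| 10% | 30% | 0.5 | 0.50 | 0.40 |

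First row in full: 0.30×0.90 + 0.5×(0.30×0.10 + 0.70×0.90) = 0.27 + 0.33 = 0.60. Deaths ranked worst: 0.10×0.70 + 0.33 = 0.40. Here q = 1 means that all deaths precede any discharge. The value 0.79 is Φ(ln 2/(0.6√2)), from assumed lognormal stays with log-SD 0.6, median 10 days for survivors and 5 days to death. A simulation at 12 per arm (survivors as above, deaths on days 1 to 3, 10% versus 30% mortality) also gave 0.60 and 0.40, with the median stay about 2.2 days shorter in the arm with more deaths.

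**Binary outcomes: estimate.** The Hodges-Lehmann shift is the median of the 144 pairwise differences.
- 1/12 versus 4/12: 4×11 = 44 differences of +1, 8×1 = 8 of −1, and 92 of 0. Shift 0; risk difference 0.25 (Newcombe 95% CI −0.08 to 0.53).
- 2/12 versus 6/12: 60, 12 and 72. Shift 0; risk difference 0.33.
- 1/12 versus 7/12: 77 of 144 are +1. Shift 1; risk difference 0.50.

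The shift jumps from 0 to 1 and follows no quantity of interest.

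**Binary outcomes: p-value.** For 0/12 versus 4/12, the Mann-Whitney normal approximation (tie and continuity corrected) gives p = 0.036. Fisher's exact test gives 2×C(12,4)/C(24,4) = 2×495/10,626 = 0.093. An unconditional exact test (Barnard) gives 0.038. I also summed the binomial probabilities of all 13×13 possible tables with p < 0.05 when both arms share one event rate. The approximate test rejects in 1.5% of trials at a 10% event rate, 4.9% at 30% and 6.4% at 50%. Fisher's test rejects in 0.2%, 1.7% and 2.3%.

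**The case against.** The strongest reply is that this is a condensed article and "The statistical analysis plan can be accessed through the corresponding author". That plan is not shown and may settle how deaths enter durations and which method serves binary outcomes. This stands as a limit. The article does, however, state a rule, and that rule fits part of its own outcome list badly.

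Several stronger readings are tempting and should not be drawn:
- **One identical test for every secondary outcome.** The sentence says similar analyses, for efficacy data. Physiology has a separate rule, and safety is not plainly efficacy data.
- **No usable estimate for yes/no outcomes.** On 0/1 data, U/(n1·n2) − 0.5 is half the risk difference: at 1/12 versus 4/12, (44 + 46)/144 − 0.5 = 0.125. Nothing prevents counts being reported beside the test.
- **A fault in the test shown by 0.036 against 0.093.** An exact Mann-Whitney test on 0/1 data is in essence Fisher's test, and the article names no approximation. Much of the gap is Fisher's conservatism, as Barnard's 0.038 shows. What remains is that the p-value depends on a computing choice and that the approximate version can exceed 5%.
- **A reversal that must occur.** It needs deaths that are both early and unequal between arms. Mortality is also a listed outcome, so a reader could set the stays beside the deaths.
- **A Discussion that concedes only estimation is realistic.** It says that no definitive answer on mortality and intubation is expected, and does not mention estimation.
- **A required death score for the 3-month questionnaires.** Comparing survivors with mortality reported alongside is also defensible, so none is prescribed here.

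**Conclusion.** The point holds as an inexpensive improvement to the secondary analyses. Applied literally to length of stay and ventilation duration, the stated rule rewards early death. At 10% versus 30% mortality the probability of a better ECCO2R result is 0.60, against 0.40 with deaths ranked worst, so the direction reverses. That is the limiting case: the figure falls to 0.56 when the median time to death is 5 days against a 10-day survivor stay. It is 0.50 when deaths come as late as discharges or when mortality is equal. The mortality rates and stay distributions are assumptions.

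For yes/no outcomes the rank test is a poor default. Its usual shift estimate can be 0 with a risk difference of 0.25 or 0.33, and its large-sample p-value cannot be relied on at 12 per arm. The departure from 5% is modest (up to 6.4%).

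**What to change.** Reword the sentence so that the Mann-Whitney approach covers continuous and ordinal secondary outcomes only, and add two rules.

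1. **Length of stay and ventilation duration:** rank in-hospital deaths worst, or use ICU-free and ventilator-free days over a named period with death scored 0. Show survivors' stay descriptively.
2. **Mortality, intubation, tracheostomy and readmission:** report counts per arm with a risk difference and an exact or score 95% confidence interval. If a p-value is wanted, use Fisher's exact test and accept that it is conservative.

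The cost is wording in the analysis plan. These rules use durations, deaths and events that the article already lists. Days alive and out of hospital to 3 months would need more, because the article lists a readmission rate but not the length of readmissions.

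The downside is that the duration becomes a composite with death and no longer measures resource use alone. Raw stay should therefore still be reported for the cost analysis. If the unseen analysis plan already contains these rules, the article's sentence only needs to be brought into line with it.

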**Methods/design:**

A randomised controlled open label trial of patients (12 in each arm) with acute exacerbations of COPD at risk of failing conventional therapy (NIV) randomised to either remaining on NIV or having ECCO_2_R added to NIV with a primary endpoint of time to cessation of NIV. The change in respiratory physiology following the application of ECCO_2_R and/or NIV will be measured using electrical impedance tomography, oesophageal pressure and parasternal electromyography. Additional outcomes, including patient tolerance, outcomes, need for readmission, changes in blood gases and biochemistry and procedural complications, will be measured. Physiological changes will be compared within one patient over time and between the two groups. Healthcare costs in the UK system will also be compared between the two groups.

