## Sample size

It is estimated that the effect of addition of ECCO_2_R will be a reduction in NIV duration from 48 h to 36 h. Group sample sizes of 24 (12 in each arm) patients achieve 80% power to reject the null hypothesis of equal means when the population mean difference is 12 h with a common standard deviation of 10 h with alpha level of 5%.

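### A one-value-per-patient Mann-Whitney test is extended to serially measured vital signs and blood gases, with no per-patient summary and no use of T0 fixed

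*Protocol article*

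**What the plan says.** In the Statistical analysis section, NIV duration "will be analysed on randomized patients using a non-parametric approach, Mann-Whitney U test". The next sentence carries that method over: "Similar analyses as for the primary outcome measure will be conducted for secondary efficacy data".

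The Secondary outcome section lists, under physiology, respiratory rate, heart rate, blood pressure, temperature and "arterial blood gases measured at time (T)0 min, T30 minutes, T 60 min, then every fourth hour for the first 24 h". Readings are six-hourly after that, until the acute phase ends.

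Three other sentences bear on these data:

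- Abstract, Methods/design: "Physiological changes will be compared within one patient over time and between the two groups".
- Statistical analysis: "Physiological data will be compared within individuals to describe a relative change in work of breathing".
- Statistical analysis: "Analysis of the physiological data will be per protocol, whilst analysis of outcomes will be intention to treat".

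A separate statistical analysis plan is said to be available on request; it is not shown here.

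**The concern.** NIV duration is one number per patient, and a Mann-Whitney test suits it. A blood gas variable is a series with its own baseline. Before a two-sample rank test can be run, someone must decide what single number represents each patient: one reading, a mean, a change from T0, or each time point in turn. The blanket sentence leaves this open, and the options differ greatly in power and in false-positive rate.

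This matters more here than in most trials. The Discussion says that 24 patients will not settle mortality or intubation and that the detailed physiology is where understanding should improve. The section on the data monitoring committee also describes the endpoints as mainly physiological. If the between-arm comparison of gases and vital signs is chosen after the data are seen, or made on one unadjusted snapshot, a real effect may be missed or may appear only at one isolated time.

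**Working it through.** **1. The plan's own figure.** The Sample size section states that "Group sample sizes of 24 (12 in each arm) patients achieve 80% power" for a 12 h difference with SD 10 h at 5% alpha. The standardised effect is 12/10 = 1.2. A two-sided two-sample t-test with 12 per arm gives 80.2% power (required n 11.94 per arm), so the figure reproduces. It concerns the primary outcome only. It supplies the 12 per arm and the only standardised effect in the document.

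**2. Readings per patient in the first 24 h, after T0.**

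- Four-hourly clock from T0: 30 min, 60 min, 4, 8, 12, 16, 20, 24 h = 8.
- Four-hourly clock from 60 min: 30 min, 60 min, 5, 9, 13, 17, 21 h = 7.

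**3. Variance of each candidate summary.** Assume unit SD and equal correlation ρ between all times, including T0. With k post-baseline readings:

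- one reading: 1
- mean of k: M = (1 + (k−1)ρ)/k
- mean minus T0: M + 1 − 2ρ
- mean adjusted for T0: M − ρ²

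| k = 8 | ρ = 0.3 | ρ = 0.5 | ρ = 0.7 |
|---|---|---|---|
| One reading | 1 | 1 | 1 |
| Mean | 3.1/8 = 0.39 | 4.5/8 = 0.56 | 5.9/8 = 0.74 |
| Mean minus T0 | 0.39 + 0.40 = 0.79 | 0.56 + 0 = 0.56 | 0.74 − 0.40 = 0.34 |
| Mean adjusted for T0 | 0.39 − 0.09 = 0.30 | 0.56 − 0.25 = 0.31 | 0.74 − 0.49 = 0.25 |

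The adjusted mean therefore has 0.25 to 0.31 of the variance of one reading. With k = 7 the last row becomes 2.8/7 − 0.09 = 0.31, 4/7 − 0.25 = 0.32 and 5.2/7 − 0.49 = 0.25. Whether there are 7 or 8 readings hardly matters.

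**4. Power.** The document gives no effect size, SD or correlation for these variables, so all three are assumed. The simulation used normal data, 12 per arm, two-sided 5%, an effect constant over 8 readings and ρ from 0.3 to 0.7. Figures are rounded, and repeat runs differ by one or two points.

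| Effect (SD) | MW, one reading | MW, unadjusted mean | MW, mean minus T0 | ANCOVA, mean adjusted for T0 |
|---|---|---|---|---|
| 0.5 | about 20% | 25–44% | 24–46% | 54–61% |
| 0.8 | about 43% | 55–82% | 52–87% | 91–96% |
| 1.0 | about 61% | 74–95% | 72–97% | 98–99% |
| 1.2 | about 77% | 87–99% | 86–99% | over 99% |

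MW = Mann-Whitney. If correlation instead decays with time (0.7 or 0.9 per 4 h), one reading has 44% power at 0.8 SD and the adjusted mean 93–98%. Under no effect, rejection was about 4.4% for Mann-Whitney on one reading and 4.6–5.6% for ANCOVA, so the gain is not bought with type I error.

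**5. Testing at every time instead.** With 8 Mann-Whitney tests per variable and no true effect, the chance of at least one p < 0.05 is 28%, 24% and 19% at ρ = 0.3, 0.5 and 0.7. That is for each variable, before counting the several variables.

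**The case against.** **A reader might infer that the plan discards T0 and all but one of the first-day readings.** No sentence says so. The blanket sentence could equally cover a Mann-Whitney test on a per-patient mean, area or change from T0, and the Abstract's reference to changes points towards a change score. This stands. The defect is that the choice is not fixed, not that a bad choice has been made.

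**A reader might also infer that the plan more than halves power.** That holds only if one unadjusted reading is used and the effect is about 0.8 SD or less. The ratio of single-reading to ANCOVA power is about 0.6 at 1.0 SD and about 0.77 at 1.2 SD. Most of the loss comes from using a single reading, not from ranks as such.

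**The sentence may not govern these variables.** It speaks of secondary efficacy data, while the section treats physiological data separately, per protocol and within individuals. The ambiguity is real but does not remove the point. The within-individual sentence concerns work of breathing and names no comparison between arms. If gases and vital signs fall under it, the between-group comparison planned in the Abstract has no stated method at all.

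**The detail may be in the unseen analysis plan.** It may, and missing detail alone would be no finding. What can be criticised is the published rule, which applies a single-value test to a list containing series.

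**The constant-effect model flatters averaging.** This partly stands. Both arms are titrated to the same pH and respiratory-rate targets, so arm differences in those two variables may shrink with time. It is a reason for an early, pre-stated window.

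**Conclusion.** The point holds in a limited form. The only between-arm method named is a one-value-per-patient test. A blanket sentence extends it to secondary outcomes that include series with a baseline, without saying what the single value is or whether T0 is used.

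The size depends on how the sentence is carried out. Under the assumptions above and at 0.8 SD, power ranges from about 43% (one reading), through 52–87% (mean change) and 55–82% (unadjusted mean), to 91–96% (T0-adjusted mean). The adjusted analysis was at least as good as every Mann-Whitney version examined. Its advantage is small where the effect is large, or where a change score is used with high correlation. These figures rest on assumed effects and correlations, normal data and a constant effect; none comes from the documents.

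The primary outcome and its stated 80% power are untouched. This is a worthwhile and cheap improvement to the secondary analyses, not a threat to the trial's main result.

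**What to change.** Limit the blanket Mann-Whitney sentence to secondary outcomes with one value per patient, such as length of stay. Add a sentence for the serial variables, named individually so that it is clear which rule covers them:

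- one between-arm contrast per variable, averaged over a pre-stated early window (shorter for pH and respiratory rate, given the common titration targets);
- estimated either from a repeated-measures model with arm, time, arm-by-time and the patient's T0 value as covariate, or from an ANCOVA of the per-patient mean on arm and T0;
- a small-sample degrees-of-freedom correction for the repeated-measures model;
- results at individual times shown descriptively, not as separate tests.

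If a rank test is preferred throughout, naming the mean change from T0 over the window as the per-patient value would be an acceptable second choice, weaker when correlation is low.

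The cost is wording in the protocol or analysis plan; every reading is already scheduled. The downside is a model assumption with 24 patients, which a permutation p-value for the same contrast can check.
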